### Study Design

This is an 18-month, prospective, multicenter, open-label study with 3 parallel arms, using randomization and control to assess a range of oral health and dental esthetic metrics (Figure 1). The primary objective is to compare these metrics between cigarette smokers transitioning to C-F NA and those who continue smoking.

Eligible smokers will be allocated randomly to either the control group (arm A), which will receive standard care inclusive of cessation counseling (ie, very brief advice [VBA]) or the intervention group (arm B), which will be given a C-F NA of their choice and will also receive VBA. Individuals who have never smoked will form a reference group (arm C). Throughout the study, participants from all 3 groups will undergo regular assessments of their oral health and dental esthetic. The study will be conducted in 4 dental clinics across 4 different countries (Italy, Poland, Moldova, and Indonesia).

The study protocol adheres to the guidelines stipulated by the Standard Protocol Items: Recommendations for Interventional Trials (SPIRIT) guidelines.

**Figure 1 figure1:**
[figure not shown]
Study design. Smokers not intending to quit and without clinical signs of periodontitis were randomized to either standard care (arm A) or combustion-free nicotine alternatives (C-F NA; arm B). A reference group of never smokers will also be included but not randomized (arm C). Participants were prospectively reviewed at 4 dental clinics for cigarette consumption and C-F NA use, oral health and dental esthetic measurements, vital signs, and adverse events for up to 18 months.

The study flow is illustrated in Figure 2.

All participants will attend a total of 7 clinic visits: day −28 to day −1—screening; day 0—enrollment and randomization (visit 0); day 14—baseline visit (visit 1); day 90—week 12 (visit 2); day 180—week 24 (visit 3); day 360—week 52 (visit 4); day 540—week 76 (visit 5).

**Figure 2 figure2:**
[figure not shown]
Study flow diagram of study participants. C-F NA: combustion-free nicotine alternatives.

Screening visits will be performed within 28 days before enrollment to verify the eligibility criteria (visit 0; Figure 2). During the screening visit, sociodemographic data, medical and oral health history, detailed information about nicotine and tobacco consumption, and interest in trying C-F NA will be recorded. Screening for periodontal disease will be performed to exclude periodontitis, as per the definition of the guidelines of the 2017 Classification of Periodontal and Peri-implant Diseases and Conditions [28]. Smokers will be offered a smoking cessation program as per local guidelines. Any smokers who express the intention of booking for the cessation program or to quit smoking in the next 6 months will be urged to do so and will not be recruited in the study. Participants taking part in the study will be informed that they are free to quit smoking and withdraw from the study at any time. Moreover, smokers will be encouraged to quit smoking at every contact throughout the study.

Within 28 days of the screening visit, eligible participants will be invited to attend an enrollment visit (visit 0). Inclusion and exclusion criteria will be verified again. Smokers will be reminded of the risks associated with smoking before enrollment in the study and that they are free to voluntarily quit smoking and nicotine or withdraw from the study at any time. All participants will undergo a series of measurements (Tables 1-3) followed by dental scaling and polishing procedures to remove calculus, plaque, and stain.

Smokers not intending to quit will then be randomly assigned to either the control (arm A) or the intervention (arm B) group. The randomization sequence will be generated by a computer, with an allocation ratio of 1:4 (arm A: arm B) to accommodate for the estimated 25% proportion of participants achieving a sustained reduction in cigarette consumption of at least 90% in arm B (as detailed in the Statistical Considerations section). Smokers in the control group (arm A) will receive standard care, inclusive of cessation counseling (ie, VBA) at each study visit. Smokers in the intervention group (arm B) will have the option to try and choose a preferred C-F NA (ECs and HTPs) from a given pool of popular options present in the respective markets and will also receive VBA.

Individuals who have never smoked will be allocated to the reference group (arm C). Never smokers in the reference group will serve as comparators for assessing any background changes in the primary study end point (ie, Modified Gingival Index [MGI]) that may occur over time. Although never smokers will not undergo randomization, efforts will be made to achieve a comparable distribution of sex and age across all study arms.

The trial is designed as an unblinded trial because of the nature of the intervention, where participants and trial staff cannot be blinded to the specific intervention being provided. However, data analyses will be conducted blind to study arms allocation. All other trial staff who have access to outcome data will remain blinded until prespecified data analyses will be completed.

Baseline measurements will be performed at visit 1 (baseline visit) and 14 days after scaling and polishing procedures at enrollment (visit 0). Study measurements will include MGI assessment, plaque imaging, dental shade quantitation, tooth stain scores, and oral health–related quality of life questionnaires (Tables 1-3).

Smokers in arm B will be provided with a C-F NA of their choice. They will receive training and counseling on how to use the chosen C-F NA and will be provided with a full 2-week supply of the required consumables (cartridges or pods or e-liquid refill bottles for ECs and tobacco sticks for HTPs). Participants wishing to use an HTP will receive one kit and a supply of tobacco sticks of their choice. They will receive the number of tobacco sticks per day corresponding to the number of cigarettes smoked per day at baseline. Participants wishing to use a vaping product will receive one vaping kit and a supply of e-liquids of their choice. Products will be supplied at each subsequent visit throughout the study according to the study product supply schedule in Table 4.

After the baseline visit, participants will be invited to attend 4 more clinical visits (visits 2-5) to repeat study measurements (Tables 1-3).

Throughout the study, monitoring of cigarette consumption, daily C-F NA use, and oral hygiene routine will be carried out regularly using the tracker app and personal diaries. Monitoring of cigarette consumption and daily C-F NA use will also be achieved by asking participants in arm B to return all empty, partly used, and unused consumables (tobacco sticks, EC cartridges, and e-liquid refill bottles) at each study visit. The tracker app will also identify any protocol violations, collect adverse events (AEs), and send reminders (eg, next scheduled appointment, study restrictions, and instructions) throughout the study duration. The use of a dedicated tracker app adds an innovative element to continuously collect data and enhances adherence to the study protocol.

Before each study visit (visits 1-5), all participants will be required to refrain from scaling and polishing procedures, avoid modifying their habitual oral hygiene (eg, mouthwash, mouth rinse, and interdental floss), refrain from flossing for at least 72 hours before each study visit, refrain from mouth rinsing for at least 24 hours before each study visit, refrain from tooth brushing for at least 2 hours before each study visit, refrain from eating and drinking (except water) for at least 2 hours before each visit, and abstain from smoking for 2 hours before each visit. This is to minimize any potential interference with study outcomes and to maintain consistency in data collection. Throughout the study, any modifications in the oral hygiene routine of participants will be recorded using the tracker app.

A detailed description of the measurements that will be specifically performed at each trial visit is provided in Multimedia Appendix 1.

**Table 1 table1:** Study schedule of procedures (control group—arm A).

Procedure	Screening	Enrollment (V0); day 0	Baseline (V1); day 14±3	Week 12 (V2); day 90±5	Week 24 (V3), day 180±7	Week 52 (V4); day 360±7	Week 76 (V5); day 540±7
Eligibility criteria check	✓	✓					
Medical and oral health Hx^a^	✓						
Smoking Hx	✓						
Intention to quit smoking	✓						
Smoking cessation advice	✓	✓	✓	✓	✓	✓	✓
Cigarette consumption	✓	✓	✓	✓	✓	✓	✓
Exhaled CO^b^	✓	✓	✓	✓	✓	✓	✓
Interest to switch to C-F NA^c^	✓						
Informed consent		✓					
FTND^d^		✓					
Oral hygiene check	✓	✓	✓	✓	✓	✓	✓
Periodontal examination	✓						
Scaling and polishing		✓					✓
Randomization		✓					
Tracker app installation		✓					
BP^e^, HR^f^, weight, height, and BMI		✓	✓	✓	✓	✓	✓
MGI^g^ assessment		✓	✓	✓	✓	✓	✓
Plaque score imaging		✓	✓	✓	✓	✓	✓
Dental shade quantitation		✓	✓	✓	✓	✓	✓
Tooth stain assessment		✓	✓	✓	✓	✓	✓
QoL^h^ questionnaires (OHQoL^i^ and EQ VAS^j^)		✓	✓	✓	✓	✓	✓
Safety reporting		✓	✓	✓	✓	✓	✓

^a^Hx: history.

^b^CO: carbon monoxide.

^c^C-F NA: combustion-free nicotine alternatives.

^d^FTND: Fagerström Test for Nicotine Dependence.

^e^BP: blood pressure.

^f^HR: heart rate.

^g^MGI: Modified Gingival Index.

^h^QoL: Quality of Life.

^i^OHQoL: Oral Health Quality of Life.

^j^EQ VAS: EuroQoL Visual Analog Scale.

**Table 2 table2:** Study schedule of procedures (intervention group—arm B).

Procedure	Screening	Enrollment (V0); day 0	Baseline (V1); day 14±3	Week 12 (V2); day 90±5	Week 24 (V3); day 180±7	Week 52 (V4); day 360±7	Week 76 (V5); day 540±7
Eligibility criteria check	✓	✓					
Medical and oral health Hx^a^	✓						
Smoking Hx	✓						
Intention to quit smoking	✓						
Smoking cessation advice	✓	✓	✓	✓	✓	✓	✓
Cigarette consumption	✓	✓	✓	✓	✓	✓	✓
Exhaled CO^b^	✓	✓	✓	✓	✓	✓	✓
Interest to switch to C-F NA^c^	✓						
Informed consent		✓					
FTND^d^		✓					
Oral hygiene check	✓	✓	✓	✓	✓	✓	✓
Periodontal examination	✓						
Scaling and polishing		✓					✓
Randomization		✓					
Familiarization with C-F NA			✓				
C-F NA use				✓	✓	✓	✓
Tracker app installation		✓					
BP^e^, HR^f^, weight, height, and BMI		✓	✓	✓	✓	✓	✓
MGI^g^ assessment		✓	✓	✓	✓	✓	✓
Plaque score imaging		✓	✓	✓	✓	✓	✓
Dental shade quantitation		✓	✓	✓	✓	✓	✓
Tooth stain assessment		✓	✓	✓	✓	✓	✓
QoL^h^ questionnaires (OHQoL^i^ and EQ VAS^j^)		✓	✓	✓	✓	✓	✓
Safety reporting		✓	✓	✓	✓	✓	✓

^a^Hx: history.

^b^CO: carbon monoxide.

^c^C-F NA: combustion-free nicotine alternatives.

^d^FTND: Fagerström Test for Nicotine Dependence.

^e^BP: blood pressure.

^f^HR: heart rate.

^g^MGI: Modified Gingival Index.

^h^QoL: Quality of Life.

^i^OHQoL: Oral Health Quality of Life.

^j^EQ VAS: EuroQoL Visual Analog Scale.

**Table 3 table3:** Study schedule of procedures (reference group—arm C).

Procedure	Screening	Enrollment (V0); day 0	Baseline (V1); day 14±3	Week 12 (V2); day 90±5	Week 24 (V3); day 180±7	Week 52 (V4); day 360±7	Week 76 (V5); day 540±7
Eligibility criteria check	✓	✓					
Medical and oral health Hx^a^	✓						
Smoking Hx	✓						
Cigarette consumption	✓	✓	✓	✓	✓	✓	✓
Exhaled CO^b^	✓						
Informed consent		✓					
Oral hygiene check	✓	✓	✓	✓	✓	✓	✓
Periodontal examination	✓						
Scaling and polishing		✓					✓
Assignment to arm C		✓					
Tracker app installation		✓					
BP^c^, HR^d^, weight, height, and BMI		✓	✓	✓	✓	✓	✓
MGI^e^ assessment		✓	✓	✓	✓	✓	✓
Plaque score imaging		✓	✓	✓	✓	✓	✓
Dental shade quantitation		✓	✓	✓	✓	✓	✓
Tooth stain assessment		✓	✓	✓	✓	✓	✓
QoL^f^ questionnaires (OHQoL^g^ and EQ VAS^h^)		✓	✓	✓	✓	✓	✓
Safety reporting		✓	✓	✓	✓	✓	✓

^a^Hx: history.

^b^CO: carbon monoxide.

^c^BP: blood pressure.

^d^HR: heart rate.

^e^MGI: Modified Gingival Index.

^f^QoL: Quality of Life.

^g^OHQoL: Oral Health Quality of Life.

^h^EQ VAS: EuroQoL Visual Analog Scale.

**Table 4 table4:** Study schedule of combustion-free nicotine alternatives (C-F NA) supply and use checks (only for arm B).

Procedure	Screening	Enrollment (V0)	Baseline (V1)	Week											
				4	8	12 (V2)	20	24 (V3)	32	40	48	52 (V4)	60	68	76 (V5)
C-F NA use			✓	✓	✓	✓	✓	✓	✓	✓	✓	✓	✓	✓	✓
Provide C-F NA device			✓												
Hand out 2 weeks supply of consumables^b^			✓												
Hand out 4 weeks supply of consumables^a^				✓	✓		✓				✓				
Hand out 2×4 weeks supply of consumables^b^						✓		✓	✓	✓		✓	✓	✓	✓
Product use checks (collect used and unused consumables^b^)				✓	✓	✓	✓	✓	✓	✓	✓	✓	✓	✓	✓

^a^Participants wishing to use a heated tobacco product will receive one kit and supply of tobacco sticks of their choice; they will receive the number of tobacco sticks per day corresponding to the number of cigarettes smoked per day at baseline. Participants wishing to use a vaping product will receive one vaping kit and supply of e-liquids of their choice.

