### Study Measurements and Calibration

A detailed description of the study measurements that will be specifically carried out at the dental clinic is provided in Multimedia Appendix 2.

All assessors will be trained on MGI scoring, tooth stain assessment, and the correct use of technologies and software used to quantify dental plaque, tooth discoloration, exhaled carbon monoxide monitoring, and electronic case report form (eCRF) use. Assessors will be periodically calibrated on MGI scoring and tooth stain assessment. To ensure consistency in the measurements, the same assessor will collect all study end points in the same participant over the entire study period.

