The study design incorporates several significant and groundbreaking characteristics. First, we aim to enhance adherence to C-F NA and optimize overall compliance with the study’s instructions through the provision of a diverse range of products, encompassing the most popular options available in the market. This approach allows participants to tailor their own gratifying “nicotine experience” by selecting the C-F NA that aligns with their preferences. By doing so, we anticipate not only fostering a transition to the latest technology but also facilitating the reduction of cigarette smoking and bolstering long-term prevention of relapse [38-42]. It is worth highlighting that this aspect of personal choice is notably absent in studies of harm reduction. Furthermore, it is important to emphasize that the outcomes of this research will not be product specific, thereby minimizing constraints on generalizability.

Second, the study is being run in many different locations across the globe and so the challenge was to find a primary end point that could be measured by different operators in different sites, using a standardized measurement system that has been used previously and so has provenance. The index to be used had to be simple, reproducible, and relatively easy to compare between different sites and different operators. Ideally, the assessors should be able to calibrate the index to be used and compare the calibration results. The MGI is a widely used industry-standard index to determine changes in the gingival health of volunteers in clinical studies [29,43,44]. This index is simple, noninvasive, and reproducible, and it is hoped that it will be possible to train different examiners in different locations to align their assessments, thus making the results comparable. As the MGI is noninvasive, there is no gingival probing, and it is thought to be easier to calibrate examiners and compare kappa scores. Although subjective in nature, the lack of probing removes one of the variables present in using pressure to probe the gingivae. It is also thought to afford greater sensitivity in determining therapeutic efficacy [45]. This study will be the first to investigate the long-term impact of smoking or C-F NA intervention on MGI.

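### The reason given for not blinding trial staff does not extend to the examiner who scores the subjective primary end point, and no section says that this examiner is masked

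*Protocol article*

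**What the plan says.** All of this comes from the protocol article.

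- **Study Design, on blinding.** The trial is unblinded because of the nature of the intervention: "participants and trial staff cannot be blinded to the specific intervention being provided". Two sentences on masking follow: "However, data analyses will be conducted blind to study arms allocation", and "All other trial staff who have access to outcome data will remain blinded until prespecified data analyses will be completed". Neither names the clinical assessors.
- **Discussion, Overview, on the MGI.** "Although subjective in nature, the lack of probing removes one of the variables present in using pressure to probe the gingivae".
- **Study Measurements and Calibration.** For consistency, "the same assessor will collect all study end points in the same participant over the entire study period". Assessors are trained and periodically calibrated on MGI and stain scoring. Their training also covers "exhaled carbon monoxide monitoring, and electronic case report form (eCRF) use".
- **Study Design, on visits.** Monitoring of use includes "asking participants in arm B to return all empty, partly used, and unused consumables" at study visits. Randomization is on day 0 and the baseline MGI on day 14.
- **Sample Size Calculation.** The design rests on an MGI difference of 0.10 with SD 0.21.

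**The concern.** The stated reason is wider than the fact behind it. A participant who is handed a device knows it, and so does the person who hands it over. Someone who only inspects the gums need not know. The article moves from the first fact to trial staff in general and then promises masking at the analysis stage. Bias in a clinical score enters earlier, when the score is given.

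The exposure matters because the primary end point is a visual judgement and the target difference is small: 0.10, or 0.10/0.21 = 0.48 SD. If assessors know the arm and score accordingly, the resulting difference cannot be told apart from an effect of the product. The stated safeguards act on other problems. Calibration improves agreement between assessors, and keeping the same assessor within a participant removes constant leniency from the change score. Neither acts on scoring that depends on the arm.

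**Working it through.** **Inputs.** Difference 0.10, SD 0.21, 5% level, 90% power, 77 evaluable per group, 20% dropout, 92 + 368 randomized (Sample Size Calculation); two-sided t test if the data are normal (Statistical Analyses). The bias values are assumptions, because the article gives none.

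**Step 1: the plan's own figure.** The standard error for 77 v 77 is 0.21 × √(2/77) = 0.0338, so the noncentrality is 0.10/0.0338 = 2.95. The exact noncentral t calculation, one-sided at 5%, gives power 0.903, and 77 is the smallest n that reaches 0.90. The same calculation reproduces all 15 cells of Table 5. The figure of 77 is confirmed on the article's one-sided basis.

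**Step 2: which bias survives.** Let b(arm, visit) be the mean scoring error. The bias in the comparison of changes is

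[b(A, month 18) − b(A, day 14)] − [b(B, month 18) − b(B, day 14)].

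Constant assessor leniency cancels. Because the day 14 baseline follows randomization, an arm-related shift of the same size at both visits cancels too. What remains is a shift that differs by arm and changes between day 14 and month 18. That can happen: Table 4 starts product hand-out at the baseline visit and return of consumables at week 4, so knowledge of the arm may grow after baseline.

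**Step 3: two analysis sizes.** 77 v 77 is the article's evaluable design. 74 v 294 is all randomized participants less 20% (92 × 0.8 = 73.6; 368 × 0.8 = 294.4). The standard error for the second is 0.21 × √(1/74 + 1/294) = 0.0273.

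**Step 4: false-positive rate with no true effect.** This is the rejection probability of the two-sided 5% t test, with noncentrality equal to net shift / standard error.

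| Net shift towards arm B | 77 v 77 | 74 v 294 |
|---|---|---|
| 0 | 5.0% | 5.0% |
| 0.02 | 9.0% | 11.3% |
| 0.03 | 14.3% | 19.5% |
| 0.05 | 31.2% | 44.7% |
| 0.10 | 83.5% | 95.5% |

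The smallest observed difference that reaches significance is 0.067 (77 v 77) or 0.054 (74 v 294). A net shift of that size makes significance about as likely as not. On the one-sided test used for sizing, a shift of 0.03 gives 22% and 29%, and 0.05 gives 43% and 57%.

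**The case against.** Several stronger readings are tempting, and the article does not support them.

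- **That the MGI scorer is unmasked by design.** The Study Design section also says that other staff with access to outcome data stay blinded. The sentence is ambiguous. The word *other* sets these people apart from the staff declared unblindable, and assessors are named in neither group. The text shows that masking is unstated, not that it is absent.
- **That the scorer learns smoking status at the visit.** Assessors are trained on carbon monoxide monitoring and the eCRF. The article does not say that the person scoring MGI takes that participant's reading, or takes it first. Exhaled carbon monoxide is not a listed end point, the schedules give no order within a visit, and the appendices that describe visit activities are not shown. Assessors may learn it; that they do is inference.
- **That one assessor scores the whole trial.** The rule applies within each participant. It helps reliability and is not in itself a source of bias between arms.
- **That modest bias could create the whole effect.** The whole design effect needs a net shift of 0.10. Shifts of 0.03 to 0.05 produce significance in a minority of trials under the two-sided test. The article gives no range for the MGI, so what counts as modest is a judgement.

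The cancellation in step 2 is also a fair limit: knowledge of the arm does harm only if its influence on scoring changes after day 14. Timing is another. Enrollment ended in June 2023, so the baseline scores are in and some assessors may already know the arm.

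What stands after all this is that the stated reason does not cover the examiner, no sentence masks the examiner, and none of the stated safeguards removes scoring bias that depends on the arm.

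**Conclusion.** The point holds in limited form. The nature of the intervention explains why participants and supply staff are unblinded, but not why an MGI or stain examiner could not be masked. As written, the article leaves a subjective primary score open to arm-dependent bias.

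If such bias produced a net shift of 0.03 in the change score, the two-sided false-positive rate would be 14% to 20% instead of 5%; at 0.05 it would be 31% to 45%. These figures assume no true effect, SD 0.21 in both arms, a t test, and shifts chosen for illustration. They show how sensitive the result is and do not estimate bias in this trial. The concern applies mainly to MGI and tooth stain, because plaque imaging and spectrophotometric shade are instrument-based.

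**What to change.** 1. In Study Design, limit the statement that blinding is impossible to participants and staff who supply the product. State that MGI and stain assessors are masked to arm, and say who the other blinded staff are.
2. At all remaining visits, have the existing assessor score MGI and stain first, before carbon monoxide, consumption questions, cessation advice and product return. Other existing site staff handle those tasks.
3. Hide arm and product fields in the assessor's eCRF view, and ask participants not to mention their product to the assessor.
4. Keep the same assessor within each participant.
5. For visits already completed, report whether the assessor was masked, and interpret MGI beside the plaque and shade results that are already planned.

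The cost is a reordering of visit tasks and a restricted eCRF view. It needs no extra assessor or procedure, provided each site has a second staff member for the revealing tasks; the article does not give site staffing. Masking will be imperfect, because stains may hint at smoking and some assessors may already know the arm. If few or no visits remain, items 1 and 5 still apply.
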